## 3. Discussion

This paper provides a comprehensive overview of the background and the study protocol for the development of innovative organizational models for tele-rehabilitation within the region of Tuscany (Italy).

An evolution of tele-medicine and tele-rehabilitation in the Italian healthcare landscape has occurred, particularly after the COVID-19 pandemic [83], with the establishment of a National Tele-rehabilitation network in 2015 by the Italian Ministry of Health. This network, involving the main Research Institutes (i.e., IRCCS), aims to promote the sharing of clinical-scientific activities and data and the development of collaborative projects to improve the prevention, diagnosis and rehabilitation of specific diseases (neurological, neuro-psychiatric, and related disorders), including neurodevelopmental disorders [84].

However, tele-rehabilitation is mainly applied within research projects and centers of excellence, with limited practical implementation in local health services where continuity of care is crucial.

So far, the available literature emphasizes the potential advantages of tele-rehabilitation, including enhanced access for individuals residing remotely or facing physical limitations [85]. Benefits also encompass time and cost savings [13], improved treatment adherence [86] and frequency [14], and the maintenance of elevated satisfaction [16]. The use of innovative technologies, such as virtual reality, allows the possibility to insert rehabilitation programs within playful and interactive scenarios, further supporting treatment adherence and motivation, especially among children. Additionally, with no doubt, tele-rehabilitation facilitates continuous treatment monitoring through the collection of quantitative data [87].

The use of these technologies is widespread in Italy and other foreign countries [88,89,90] with promising results but also showing several limitations, such as small sample sizes, which hinder the relevance of findings for economic analysis, and resistance to change among healthcare professionals due to insufficient knowledge, limited experience, and low computer literacy among health care personnel. Moreover, there is a pressing need to establish standards for procedures, protocols and objectives related to tele-rehabilitation [12,25,91]. This concern is especially critical in the developmental age, where research is comparatively limited compared to the adult population.

The lesson learned from the COVID-19 pandemic is that we can only partially apply tele-rehabilitation to daily neuro-rehabilitation routines in increasing and improving the patient’s care. There is a widespread agreement on the fact that face-to-face therapeutic interactions are an absolutely irreplaceable element in the relationship between patients and healthcare providers; however, tele-rehabilitation could act as the missing pieces of the puzzle leading to an optimal continuity of care and support a greater treatment intensity [92]. Furthermore, recent study results report that clinicians and the general population exhibit apprehension about tele-rehabilitation [93].

Considering neurodevelopmental disabilities as involving the impairment of multiple cognitive, motor and speech functions, many technological systems used in tele-rehabilitation could enable the implementation of integrated and multi-domain treatments within a unified rehabilitative setting. Thanks to the hardware and software variability of technological devices, clinicians could, therefore, choose the most effective rehabilitation solutions within the different possibilities by tailoring treatments based on specific treatment goals. However, results presented by a recent systematic review [25] showed that studies predominantly focused on the tele-rehabilitation of a single domain, specifically neuropsychological and motor functions, with less emphasis on speech therapy; only a limited number of studies addressed the simultaneous rehabilitation of multiple abilities.

In this framework, our research specifically focuses on integrating tele-rehabilitation into local health services, which is crucial for ensuring continuity of care. Additionally, while most studies have primarily addressed single-domain rehabilitation, our approach aims to integrate multi-domain treatments, thus providing a more comprehensive care model.

By incorporating tele-rehabilitation into local health services, we aim to enhance the continuity and intensity of care, particularly benefiting patients with neurodevelopmental disorders, but also the quality of care and the health care system. Health policies could use these results to develop facilities that support wider implementation of tele-rehabilitation, ensuring integration with face-to-face interactions so as to optimize the use of resources and improve patient outcomes.

However, this project faces certain limitations, including the generalizability of results across different populations or settings. Future research should address these limitations by including larger and more different sample sizes and exploring the applicability of our findings in various healthcare environments.

To the best of our knowledge, the TOSCANA TABLET project represents the first project focused on implementing tele-rehabilitation programs directly at the local level, with a specific emphasis on engaging the pediatric population. The potential effects will be not only on the patient’s care concerning the care contents but also on creating new innovative approaches and fruitful networks among professionals as a new model of care, laying the foundation for future and innovative proposals. Consequently, our effort aims to pave the way for more robust and effective tele-rehabilitation solutions that enhance patient care and support the evolving landscape of healthcare.

## 4. Conclusions

In conclusion, this study protocol aims to develop innovative organizational models to promote continuity of care through tele-rehabilitation for neuro-psychomotor and language functions in individuals with congenital and acquired developmental disabilities, with a specific emphasis on pediatric patients with neurodevelopmental disorders within the region of Tuscany, Italy.

By focusing on organizational aspects, acceptability, usability, and the performance of ICT solutions, this study seeks to fill gaps in the current literature and enhance the practical application of tele-rehabilitation within local health services. This approach aims to improve the continuity and intensity of care, thereby improving the overall quality of the healthcare system. Furthermore, a multi-domain approach can provide a more comprehensive care model, offering significant benefits for patients with neurodevelopmental disorders.

Potential effects include not only enhanced patient care but also the development of innovative approaches and collaborative networks among healthcare professionals. This will establish a novel model of care, paving the way for future innovative proposals and supporting the evolving landscape of healthcare.

## Figures and Tables

**Figure 1 jcm-13-04159-f001:**
[figure not shown]
Three main phases of TABLE TOSCANA study. A synthetic overview of the three project phases detailed in the text: implementation of technological devices, hypothesizing in the meanwhile new organizational models integrating tele-rehabilitation within conventional care pathways; systems validation through a two parallel arm, wait-list study, recruiting participants with congenital and acquired neurodevelopmental disabilities; data analysis, both considering organizational dimensions, feasibility, and efficacy results.

**Figure 2 jcm-13-04159-f002:**
[figure not shown]
New organizational models’ hypothesis. (**a**) depicts the decision-making procedure with different steps for assigning patients to one of the study arms, according to the interdisciplinary clinical assessment (using standardized tests and technological devices) and the identified treatment goals. If the designed objectives could be achievable through technology and patients meet the inclusion criteria for the Tablet Toscana project, tele-rehabilitation pathways will be initiated. (**b**) illustrates the tele-rehabilitation pathway, involving an initial familiarization phase for patients and families with the system, followed by a 3-month treatment with mixed online and offline sessions. Thus, post-treatment evaluations will be conducted to gather efficacy and feasibility data.

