#### 2.1.2. Phase II

During this phase, the validation of the implemented technologies will be conducted through a wait-list study (Figure 3) with two parallel arms. One hundred subjects (comprising 80 children and 20 young adults) will be recruited from the aforementioned clinical centers. The wait-list design study will ensure that all enrolled patients will be eligible for the experimental treatment, thus avoiding issues related to equipoise.

After the identification of eligible subjects according to inclusion and exclusion criteria (described below), participants will be stratified according to several criteria, including (i) diagnosis (congenital or acquired developmental disorder group), (ii) gross motor function classification system (GMFCS) level (GMFCS I–II/GMFCS III–IV), (iii) age group (6–10/11–15/16–20/21–30), (iv) and technology utilized (APP vs. Home Kit). Then, participants will be randomly assigned to the experimental group (EG)—receiving a 3-month tele-rehabilitation immediately—or the wait-list group (WG)—continuing traditional rehabilitation care for the same duration. All subjects will be evaluated before (T0) and after (T1) the 3-month intervention period (tele-rehabilitation or traditional rehabilitation), using standardized clinical tests. Moreover, participants enrolled in the WG will be re-evaluated at the end of the 3 months of tele-rehabilitation training (T1 plus). Finally, at the end of tele-rehabilitation training, ad-hoc questionnaires will be administered to the main stakeholders to assess the systems’ usability and acceptability. The program of enrolment, interventions and assessments designed according to SPIRIT guidelines are shown in Figure 4.

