As mentioned above, after the enrolment, participants will be stratified according to several criteria, including (i) diagnosis (congenital or acquired developmental disorder group), (ii) GMFCS level (GMFCS I-II/GMFCS III–IV), (iii) age (6–10/11–15/16–20/21–30), (iv) and technology utilized (APP vs. Home Kit). Randomization, sequence generation and preparation of group allocation materials will be carried out by an independent researcher who will not be involved in the trial. Using a computer-generated set of random numbers, they will be then allocated to experimental or control groups. Participants, parents, and clinical staff will be aware of the allocation group. Pairs will be randomly divided into two groups with a 1:1 experimental/SC (wait-list) ratio. Participants assigned to the experimental group will begin treatment with technology immediately for a 3-month period, while those in the SC group will continue with their usual care.

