### 2.7. Statistical Analyses

Descriptive statistics (means, standard deviation, frequencies) will be investigated, analyzing potential baseline differences between groups explored and computing the p values. The normal distribution of the sample will be investigated through the Shapiro–Wilk test. Subsequently, a comprehensive analysis, both qualitatively and quantitatively, will be conducted on the questionnaire data gathered from various stakeholders, aiming to assess the usability and acceptability of the devices used. Statistical analysis, such as ANOVA or regression, will be carried out to determine differences based on age, diagnosis, functional profile (cognitive and motor outcomes), and devices used during tele-rehabilitation. Furthermore, inferential analyses will be carried out to assess pre–post-treatment differences, gain efficacy data, and also consider the different devices used during tele-rehabilitation pathways. Finally, flowchart diagrams will be created to illustrate the different organizational models identified. Statistical significance will be considered at p<.05. Statistical Package for Social Sciences (SPSS) (IBM Statistic) will be adopted for carrying out the statistical analyses.

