**Figure 3 jcm-13-04159-f003:**
[figure not shown]
Flowchart of TABLET-TOSCANA study according to CONSORT guidelines. Graphical representation of the two parallel arms wait-list study, illustrating the pathway from the identification of the eligible patients, according to the inclusion and exclusion criteria, proceeding through a baseline assessment of cognitive, motor and speech-communication functions. Thus, a stratification process will be foreseen, considering different demographic, clinical and technological parameters, in order to foster the random assignment to one of the two experimental groups or to the control one. After a 3-month tele-rehabilitation program, with mixed online and offline sessions, post-treatment evaluations will be conducted.

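### The methods text and the captions of Figures 2 and 3 disagree on whether the device is randomised, which decides how the planned device comparisons can be read

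*Protocol article*

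**What the plan says.** **Methods text.** Section 2.1.2 describes "a wait-list study (Figure 3) with two parallel arms". Participants are first stratified by diagnosis, GMFCS level, age group and technology, and only then randomised to immediate tele-rehabilitation (EG) or the wait-list (WG). Section 2.4 repeats the strata and gives sequence generation to an independent researcher: "Using a computer-generated set of random numbers, they will be then allocated to experimental or control groups". It adds: "Pairs will be randomly divided into two groups with a 1:1 experimental/SC (wait-list) ratio". Pairing is explained nowhere else in the article.

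**Figure 3 caption.** The trial flowchart is introduced as showing two parallel arms. The caption then says that stratification, on technological parameters among others, serves "to foster the random assignment to one of the two experimental groups or to the control one".

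**Figure 2 caption.** Part (a) "depicts the decision-making procedure with different steps for assigning patients to one of the study arms, according to the interdisciplinary clinical assessment" and the treatment goals. If the goals can be reached with technology and the inclusion criteria are met, tele-rehabilitation begins. The caption mentions neither randomisation nor the wait-list.

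**Analysis.** Section 2.7 plans ANOVA or regression on the questionnaire data "to determine differences based on age, diagnosis, functional profile (cognitive and motor outcomes), and devices used during tele-rehabilitation". It also plans pre-post efficacy analyses that take the device into account.

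**The concern.** Taken literally, the texts differ on three things: whether chance or clinical assessment sets the arm, whether there are two groups or three, and whether the device is fixed before randomisation or assigned by it.

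The third has the most direct consequence for the analysis. Usability and acceptability are primary outcomes, and Section 2.7 compares them between devices. If the device was randomised, a difference between APP and Home Kit users can be attributed to the device. If it is a stratum, users of the two devices may differ in age, diagnosis, motor level or rehabilitation goals, and the same difference is only an association. The planned pre-post efficacy analysis by device has a further weakness: change from before to after treatment, taken by itself, includes maturation, practice on the tests and continuing usual care. The wait-list group is there to remove these.

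**Working it through.** The point is textual, so the texts come first.

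| Place | What sets the arm | Groups | Status of device |
|---|---|---|---|
| Section 2.1.2 | Chance, after stratification | 2 | Stratum, fixed beforehand |
| Section 2.4 | Chance, independent sequence, 1:1 | 2 | Stratum, fixed beforehand |
| Figure 3 caption | Chance | 2 (opening), 3 (later) | Stratification parameter; randomised if the two experimental groups are the devices |
| Figure 2 caption | Clinical assessment and goals, as worded | Not stated | Not stated |

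1. **Device.** Under Sections 2.1.2 and 2.4, a participant in the APP stratum can be randomised to EG or WG but never to the Home Kit. If the two experimental groups in Figure 3 are the devices, that participant could be randomised to either device. Both cannot hold.

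2. **What is randomised under the two-arm rule.** EG against WG overall is randomised. So is EG against WG within each device stratum, and therefore the difference between those two contrasts (the arm-by-device interaction). APP users against Home Kit users is not.

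3. **Inputs for precision.** Section 2.3 gives N = 100, a between-group t-test, d = 0.4, α = 0.05 and power 0.80. Two-sided testing is assumed, since the article does not state it. Power comes from the noncentral t distribution with noncentrality δ = d·√(n₁n₂/(n₁+n₂)) and n₁+n₂−2 degrees of freedom.

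4. **The plan's own figure.** 100 per arm gives δ = 0.4·√50 = 2.83 and power 0.80. With 50 per arm, δ = 0.4·√25 = 2.00 and power is 0.51. So 100 reproduces per arm, not as a total. That is a separate issue and matters here only because 0.51 is the baseline.

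5. **EG minus WG within device.** The device split is not stated.
   - Equal split (assumed), 25 against 25: δ = 0.4·√12.5 = 1.41, power 0.28.
   - 70:30 split (assumed): 35 against 35 gives 0.38 and 15 against 15 gives 0.18.
   - Section 2.6.2 selects tests to suit each patient, so many tests will have fewer participants than this.

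6. **Arm-by-device interaction.** With 25 per cell, its standard error is σ·√(4/25) = 0.4σ, against σ·√(2/50) = 0.2σ for the overall contrast. If the device-specific effects differ by 0.4σ, δ = 1.0 and power is about 0.17.

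7. **Three groups.** The article states no split. If it were equal, 33 against 33 gives δ = 1.62 and power 0.36 for one device against control. Pooling both devices, 67 against 33, gives δ = 1.88 and power 0.46, against 0.51 for two arms. These figures illustrate the reading and do not measure a fault in the two-arm plan.

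**The case against.** The best defence is that the allocation rule is not in doubt. The Abstract, Sections 2.1.2 and 2.4, the Figure 1 caption and the opening of the Figure 3 caption all describe a randomised wait-list comparison or two parallel arms. Section 2.1.1 introduces Figure 2 as a hypothesised organisational model from Phase I, and Section 2.1.2 cites Figures 3 and 4, not Figure 2, for trial conduct. The Figure 2 steps can be read as screening before randomisation. The two experimental groups in Figure 3 can be read as the device subgroups of EG. Only the captions could be read, and the drawings may be clearer. This stands, and it sets the limits of the point.

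A reader might infer that clinicians choose the arm and that the randomised comparison is therefore undermined. The documents do not support this. No methods section gives clinicians that choice, and Section 2.4 places the sequence with an independent researcher. A reader might also infer that the device is chosen on clinical grounds and that a device effect will be presented as causal. No passage says either, and Section 2.7 lists the device beside age and diagnosis, which are not randomised.

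The defence does not settle the device. Even on the charitable reading, Figure 3 describes assignment to the experimental groups as random, while the methods text makes the device a stratum. Nor is this a detail left to a fuller document: the article states the matter in conflicting ways.

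**Conclusion.** The point holds as a conflict over the number of groups and the status of the device, of moderate to minor severity. The two-arm 1:1 rule is clear enough to govern, and bias in the EG-WG contrast would arise only if the Figure 2 caption were applied as worded. If the device is a stratum, as the methods text has it, the device-versus-device comparisons in Section 2.7 are observational, and pre-post change by device makes no use of the wait-list control. Randomised evidence on efficacy by device is available but weak: power about 0.28 per device and 0.17 for the interaction, assuming an equal device split, two-sided α = 0.05 and a standardised effect (or difference in effects) of 0.4. It can support only exploratory statements.

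**What to change.** 1. Reconcile Sections 2.1.2 and 2.4 with the captions of Figures 2 and 3 so that one allocation rule is stated, and explain or remove the reference to pairs in Section 2.4.
2. If the two-arm rule stands, reword the Figure 2 caption as assessment of eligibility and intended device before randomisation, and the Figure 3 caption as two arms stratified by device.
3. Record the intended device before allocation in both arms. A wait-list participant has not yet used a device at that point, so the stratum has to be the intended one.
4. Estimate efficacy by device as the T0-T1 EG-minus-WG contrast within each device stratum, with an arm-by-device interaction, labelled exploratory.
5. Report device-versus-device usability differences as non-randomised, with baseline characteristics by device.

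The cost is two caption corrections, a clarified sentence and one interaction term. Stratifying by device already requires the intended device to be known before allocation, so no new data are needed.

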**Figure 3 jcm-13-04159-f003:**
[figure not shown]
Flowchart of TABLET-TOSCANA study according to CONSORT guidelines. Graphical representation of the two parallel arms wait-list study, illustrating the pathway from the identification of the eligible patients, according to the inclusion and exclusion criteria, proceeding through a baseline assessment of cognitive, motor and speech-communication functions. Thus, a stratification process will be foreseen, considering different demographic, clinical and technological parameters, in order to foster the random assignment to one of the two experimental groups or to the control one. After a 3-month tele-rehabilitation program, with mixed online and offline sessions, post-treatment evaluations will be conducted.

**Figure 4 jcm-13-04159-f004:**
[figure not shown]
Spirit Figure. Schedule of study enrolment, interventions and assessments.

**Figure 5 jcm-13-04159-f005:**
[figure not shown]
Technological devices for tele-rehabilitation purposes. (**a**) VRRS Home Kit Tablet: A case provided to patients and their families, equipped with a tablet and a set of integrated motion sensors, allowing to delivery of home tele-rehabilitation pathways. (**b**) MedicoAmico APP: A medical device directly downloadable to patients’ and families’ devices (computer, phone, tablet) to perform cognitive, speech-language, and motor interventions. Remotely monitored by the clinician.

**Figure 6 jcm-13-04159-f006:**
[figure not shown]
MedicoAmico APP exercises’ library. (**a**) Examples of motor activities implemented and now available on MedicoAmico APP. (**b**) Examples of cognitive and speech-communication exercises available within the wide library of the medical device. Parameters, including repetition, time and difficulty levels, are displayed in the upper section.

## Data Availability

The information provided in this study can be obtained by contacting the corresponding author. As of now, the data cannot be accessed publicly due to the enrolment and signing of the participants’ consent being in progress. Furthermore, our research primarily focuses on methodology, and we do not possess any clinical data regarding the patients involved.
